### 3. Objectives

#### General objectives

- Assess whether vaccine campaigns have had the expected impact on population immunity among children 6 months–14 years of age through:
  - Childhood vaccination coverage assessment
  - Serological assessment of immunity for several VPDs
- Identify barriers to accessing and utilizing vaccination services in the camps
- Assess exposure to malaria and other parasitic and neglected tropical diseases

#### Specific objectives

##### Primary

- Determine the proportion of FDMN children aged 6 months–6 years who received 0, 1, 2, or 3 doses of pentavalent vaccine and 0, 1, 2, or 3 doses of OPV in campaigns since August 2017
- Determine the proportion of FDMN children aged 1 year–6 years with protective antibody titers for poliovirus, tetanus, diphtheria, measles, and rubella
- Determine the proportion of FDMN children aged 7 years–14 years who received 0, 1, 2, or 3 doses of Td vaccine in campaigns since August 2017
- Determine the proportion of FDMN children aged 7 years–14 years with protective antibody titers for poliovirus, tetanus, diphtheria, measles, and rubella

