- Vaccination of close contacts of diphtheria cases at 19 fixed sites (January 2018);
- Planning for expansion of routine immunization service delivery to new health facilities in the FDMN settlement areas;
- Additionally, beginning in September, 2017, the following vaccination campaigns have taken place:

| Campaign                                                                         | Target Age         | Target Population | Coverage       | Remarks                                 |
|----------------------------------------------------------------------------------|--------------------|-------------------|----------------|-----------------------------------------|
| 1. MR, bOPV and Vitamin A campaign: 16 September-03 October 2017 (except Friday) |                    |                   |                |                                         |
| • MR                                                                             | 6 mons - <15 years | 122,580           | 135,519 (110%) | Card provided (1 st version) |
| • bOPV                                                                           | 0 - <5 years       | 47,168            | 72,334 (153%)  |                                         |
| • Vit-A                                                                          | 6 mons - <5 years  | 44,000            | 72,064 (164%)  |                                         |
| 2. OCV 1st round Campaign: 10-18 October 2017 (including Friday)                 |                    |                   |                |                                         |
| • OCV                                                                            | >1 year            | 658,371           | 700,487 (106%) | No Card, Soap provided                  |
| 3. OCV 2 nd round Campaign : 04-09 November 2017 (except Friday)      |                    |                   |                |                                         |
| • OCV                                                                            | >1 year - <5 years | 182,317           | 199,472 (109%) | No Card                                 |
| • bOPV                                                                           | 0 - <5 years       | 209,931           | 236,696 (103%) |                                         |

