| Campaign                                                                                                   | Target Age         | Target Population | Coverage       | Remarks                                                   |
|------------------------------------------------------------------------------------------------------------|--------------------|-------------------|----------------|-----------------------------------------------------------|
| 4. Measles and Rubella Mop up campaign: 18 November-05 December2017 (except Friday)                        |                    |                   |                |                                                           |
| MR                                                                                                         | 6 mons - <15 years | 336,943           | 354,982 (105%) | Card provided (2 nd version)                   |
| 5. Penta, PCV, bOPV & Td campaign ( 1st round) : 12 - 31 December 2017 (except Friday)                     |                    |                   |                |                                                           |
| Penta, PCV, bOPV,                                                                                          | 6 weeks - <7years  | 185,533           | 149,962 (81%)  | Card provided (2 nd & 3 rd version) |
| Td                                                                                                         | 7 - < 15 years     | 172,007           | 165,927 (96%)  |                                                           |
| 6. Penta, PCV, bOPV & Td campaign ( 2 nd round) : 27 January – 10 February 2018 (except Friday) |                    |                   |                |                                                           |
| Penta, PCV, bOPV,                                                                                          | 6 weeks - <7years  | 185,516           |                | Card provided (2 nd & 3 rd version) |
| Td                                                                                                         | 7 - < 15 years     | 178,471           |                |                                                           |

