In addition, a third round of Penta & OPV (6 weeks–7 years) and Td (7–14 years) is planned for March 2018. Upon completion of the three rounds of Pentavalent, OPV and PCV vaccination, the MOH&FW and partners plan to establish routine immunization services and conduct additional immunization campaigns as necessary in order to reach and sustain levels of

immunization coverage that protect the FDMN children from VPDs and reduce the chance of outbreaks in the settlements and surrounding host community. Although a 2015 EPI Coverage Evaluation Survey reported that 80-84% of infants in Cox's Bazar host community have received all of their scheduled vaccines, as of February 9, 2018 there have been 45 suspected diphtheria cases reported in the host community since November 2017 [3]. Bangladesh's guidelines for routine immunization do not recommend a DTP booster after three doses of DTP during infancy. Therefore, there may be a large host population living in close proximity to the FDMN settlements susceptible to VPDs as well.

In order to estimate the proportion of individuals (especially the recent arrivals) that remain un- or under-protected against the diseases targeted by the vaccination efforts, we propose to conduct an assessment of vaccination coverage and a serological assessment of immunity.

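### The primary OPV outcome stops at 3 doses, but the protocol's own campaign list allows 4 or 5 in its counting window, and a count of 3 does not identify the three joint Penta/OPV rounds

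*Protocol*

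**What the plan says.** Protocol section 3 (Specific objectives, Primary) sets the outcome for ages 6 months–6 years as "0, 1, 2, or 3 doses of pentavalent vaccine and 0, 1, 2, or 3 doses of OPV in campaigns since August 2017". Pentavalent and OPV share one scale and one counting window.

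The campaign table in section 2 lists oral polio vaccine four times in that window:

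- Campaign 1, "1. MR, bOPV and Vitamin A campaign: 16 September-03 October 2017 (except Friday"): bOPV for children from birth to under 5 years.
- Campaign 3, the second cholera vaccine round, "round Campaign : 04-09 November 2017 (except Friday"): bOPV for the same age range.
- Campaign 5, "5. Penta, PCV, bOPV & Td campaign ( 1st round) : 12 - 31 December 2017 (except Friday"): bOPV with Penta and PCV, from 6 weeks to under 7 years.
- Campaign 6, the second such round, "round) : 27 January – 10 February 2018 (except Friday"): the same vaccines and age range.

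The text after the table adds that "a third round of Penta & OPV (6 weeks–7 years) and Td (7–14 years) is planned for March 2018". Section 8 places data collection in April–May 2018, after that planned round.

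The analysis plan in section 10 has a row for vaccine doses and a separate row for campaign participation, both by antigen, overall and by camp and age group. It gives no dose categories and no rule for a fourth or fifth OPV dose.

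**The concern.** The OPV categories appear to follow the three-round pentavalent schedule, while the stated window also takes in the two autumn 2017 campaigns that gave OPV without pentavalent. The categories are therefore not exhaustive. A child under 5 who was reached every time has more doses than the top category allows.

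The analyst would have to choose a rule the objective does not give: leave such children out, pool them into 3, or count only some campaigns. Each choice gives a different primary result. Under pooling, a child reached in all five rounds and one who missed two share a category. The ceiling also differs by age within the band, because children already 5–6 in autumn 2017 were outside the target of both early campaigns.

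**Working it through.** **1. Count the OPV rounds by target age (section 2).**

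| Round | Under 5 in autumn 2017 | Already 5–6 |
|---|---|---|
| Campaign 1, Sept–Oct 2017 | yes | no |
| Campaign 3, Nov 2017 | yes | no |
| Campaign 5, Dec 2017 | yes | yes |
| Campaign 6, Jan–Feb 2018 | yes | yes |
| Third Penta/OPV round, planned March 2018 | yes | yes |
| Maximum | 4 + 1 planned = 5 | 2 + 1 planned = 3 |

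The stated top category of 3 is reproduced only for the older children, or if only the three joint rounds are counted.

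**2. Share of the band that is age-eligible.** Assume uniform ages from 6 months to under 7 years (78 months), presence throughout, and a survey on 8 April 2018. Campaign 1 began 6.7 months earlier and campaign 3 began 5.1 months earlier.

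- All five rounds: born by campaign 1 and under 5 at campaign 3, so (60 + 5.1 − 6.7)/78 = 58.4/78 = 75%.
- At least four rounds: under 5 at campaign 1, so (60 + 6.7 − 6)/78 = 60.7/78 = 78%.
- Moving the survey to 15 May, or using the end dates of the rounds, gives 75% and 77–79%.

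**3. Reach of campaign 1.** It gave 72,334 bOPV doses. The November campaign, for the same ages, gave 236,696 doses against a target of 209,931.

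- Relative to November doses: 72,334/236,696 = 0.31.
- Relative to the November target: 72,334/209,931 = 0.34.

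The November coverage is printed as 103%, but 236,696/209,931 = 113%. The targets are imprecise, so both denominators are used.

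**4. Illustrative share with 4–5 doses.** Let r be the reach of campaign 1 and p the uptake in each of the other four rounds, all independent (assumption). The only reported coverage for a joint round is 149,962/185,533 = 0.81, so p = 0.8 is used.

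P(4 or 5) = p⁴ + 4p³(1 − p)·r

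- p = 0.8: p⁴ = 0.410 and 4p³(1 − p) = 0.410. With r = 0.31 the result is 0.537; with r = 0.34 it is 0.549. That is about 54–55%.
- p = 0.7: 0.240 + 0.412r gives 0.368 to 0.380, about 37–38%.
- Four rounds only (child arrived after campaign 1): p⁴ = 41% at 0.8 and 24% at 0.7.
- March round not held: four rounds remain, and P(4) = r × 0.8³ = 0.512r = 0.16–0.17.

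**5. What a count of 3 means.** Three doses can arise from C(5,3) = 10 combinations of the five rounds, and only one of these is the three joint rounds. For a child present for four rounds with equal uptake, it is one combination in four. At p = 0.8 and r = 0.31:

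- P(exactly 3) = 0.410 × 0.69 + 6(0.8²)(0.2²) × 0.31 = 0.283 + 0.048 = 0.330.
- P(exactly the three joint rounds) = 0.8³ × 0.2 × 0.69 = 0.071.
- Share: 0.071/0.330, about 21%.

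**The case against.** The best defence is that the three joint rounds were meant. OPV stands in the same bullet as pentavalent, and section 2 speaks of completing three rounds of Penta, OPV and PCV together. On that reading 0–3 is exhaustive. It is a sensible intention, but it conflicts with the stated window of campaigns since August 2017, which takes in campaigns 1 and 3. The objective would have to say so.

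A second defence is that coding 4 or 5 doses is a tabulation rule for a statistical analysis plan that is not at hand. That would hold if the protocol were silent. Here it fixes the categories of a primary outcome, and they do not cover its own window.

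Several limits on the point do stand:

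- A reader might infer that the plan wrongly treats 3 doses as a completed OPV series. It does not. No section defines a complete series by dose number, and the objective only describes proportions.
- A reader might infer that most of the band was actually offered five doses. By target age that is about 75%. But campaign 1 was far smaller than the November campaign, the protocol stresses recent arrivals, and the fifth round was only planned. Applying one common uptake to all five rounds would overstate the problem.
- A reader might infer that receipt of the three joint rounds cannot be recovered. Campaign participation is tabulated separately by antigen and card data are also tabulated, so no loss of information is shown. Those rows still do not settle the primary categories.
- The objective makes no comparison between ages within the band. Splitting by autumn eligibility helps interpretation and does not correct an analysis error.

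**Conclusion.** The point holds as a mismatch between a primary outcome and the protocol's own campaign list. The OPV scale stops at 3, while children under 5 in autumn 2017 had four listed campaigns plus one planned round. Those with 4 or 5 doses have no category, and 3 doses cannot be read as receipt of the three joint rounds.

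The count of rounds comes directly from the protocol. The percentages are illustrations. About 54–55% of children age-eligible for all rounds would have 4–5 doses at uptake 0.8 with campaign 1 reach of 0.31–0.34, and about 41% would have four if only four rounds applied. Both rest on independent uptake. Positive dependence between rounds would raise the share reached in all four later rounds. Without the March round the figure falls to 16–17%, but then the pentavalent category of 3 would be empty as well, so the objective itself presupposes that round.

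This is a correction of wording and tabulation for one descriptive primary outcome. Sample size rests on pentavalent coverage and tetanus seroprotection, polio immunity is measured directly by neutralisation titre, and the other primary objectives are unaffected.

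**What to change.** Split the OPV part of the objective for ages 6 months–6 years in two:

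- OPV doses 0, 1, 2 or 3 in the three joint Penta/OPV rounds (December 2017, January–February 2018, and the round planned for March 2018), parallel to pentavalent.
- Total campaign OPV doses since August 2017 as 0, 1, 2, 3, 4 or 5, noting or splitting by whether the child was in the target age for the September–October and November 2017 campaigns.

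Carry the same categories into the vaccine-doses row of the analysis plan. Confirm before fieldwork that the questionnaire records OPV by campaign, because the protocol itself expects recall across several campaigns to be difficult.

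The cost is a change to the objective and table wording, plus one tablet item if OPV is not already recorded by campaign. No change to sampling or sample size is needed.

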##### Secondary

- Determine the proportion of FDMN children aged 6 months–14 years who received measles/rubella, and OCV doses in campaigns since August 2017
- Determine the proportion of FDMN children aged 7 years–14 years who received 0, 1, 2, or 3 doses of OPV in campaigns since August 2017
- Identify reasons for not being vaccinated in the last pentavalent/Td vaccination campaign among FDMN children aged 6 months–14 years
- Determine the proportion of FDMN children aged 6 months–14 years who received vaccination upon entry into Bangladesh
- Determine the proportion of FDMN children aged 6 months–14 years who received vaccination in Myanmar
- Estimate malaria parasite prevalence in children aged 1 year–14 years
- Estimate prevalence of exposure to neglected tropical diseases (e.g., lymphatic filariasis, trachoma, and yaws) in children aged 1 year–14 years

## 4. Rationale

Provision of vaccines through immunization campaigns is crucial to control outbreaks of vaccine-preventable diseases (VPDs) because they provide individual protection and herd immunity. Several vaccination campaigns, targeting primarily children under 15 years in the Forcibly Displaced Myanmar Nationals (FDMN) camps and settlements, have been conducted to reduce the risk of disease and prevent outbreaks. However, outbreaks of measles and diphtheria have been documented in these communities. To better understand the impact of vaccination activities conducted in closing immunity gaps and preventing new outbreaks, the United Nations Children's Fund (UNICEF), World Health Organization (WHO) and U.S. Centers for Disease Control and Prevention (CDC), in collaboration with the Bangladesh Government EPI Program and Institute of Epidemiology, Disease Control and Research (IEDCR), propose an assessment of vaccination coverage in a representative sample from the FDMN camps and settlements using a vaccination coverage assessment questionnaire and collection of dried blood spot (DBS) for serologic analysis of immunity.

The vaccination coverage assessment questionnaire is an excellent tool to assess vaccination coverage and identify barriers for accessing immunization, but using it to estimate gaps in population immunity will be challenging in the FDMN population because of the low retention of cards from vaccinations campaigns, difficulty recalling vaccine doses after multiple campaigns over numerous months, and the uncertainty of vaccination status in Myanmar. Thus, we propose to conduct a serological assessment by DBS simultaneously with the coverage assessment questionnaire in order to better estimate the proportion of individuals (especially among recent arrivals) that remain un- or under-protected against the diseases targeted by vaccination efforts.

Recent laboratory advances allow testing for serum antibodies for polio, other VPDs, and parasitic diseases in DBS. DBS can be collected on filter paper by fingerpricks, which require minimum amount of blood sampled and are easier to obtain from children. In addition, antibodies remain stable once dried on filter paper, and DBS are easier to process and transport in low-resource settings because they do not require centrifugation or cold chain.

The assessment of coverage and immunity will inform about the risk of additional VPD outbreaks in the camps and the threat to spread to the nearby Bangladesh host community. Data from this serosurvey can also inform about exposures to malaria, lymphatic filariasis, and yaws in camps and settlements, indicating the need for additional control programs. The results of this assessment will benefit the FDMN population by:

- 1) Providing evidence about the remaining immunity gaps among the FDMN population in order to identify VPD risks and target future vaccination efforts, both in the FDMN population as well as the nearby host Bangladesh population;
- 2) Identifying barriers to vaccination in the FDMN population, which, in turn, will help the microplanning of future immunization activities.
- 3) Provide information useful to malaria and parasitic control programs for future activities.

## **5. Methodology**

### **Overview**

We propose to select a representative sample of households in Kutupalong Registered Camp, Nayapara Registered Camp, and the makeshift/informal settlements. In the formal camps, simple random sampling of households will take place; in the makeshift/informal settlements, we will use a multi-stage cluster approach. In each selected household, we will randomly select one child 6 months–6 years of age and one child aged 7–14 years. For each child, we will conduct a short interview in Rohingya in or near the home with the available caregiver using a standardized vaccine coverage assessment questionnaire to assess vaccines received during the campaigns and elsewhere, as well as barriers for receiving vaccination during the most recent vaccination campaign. Available vaccination cards will be reviewed to record documented vaccinations received. The expected number of children to be enrolled is ~1089 children aged 6 months–6 years and ~1055 children aged 7–14 years.

In a subset of children selected for the caregiver interview (expected number of children to be enrolled: ~914 children aged 1–6 years of age and ~787 children aged 7–14 years), we will collect 3–4 drops of blood using a single fingerprick. The drops of blood will be applied to filter paper for determination of antibodies to select VPDs. The dried blood spots contained in paper filters will be stored in Ziploc bags and plastic containers with desiccant bags to protect against humidity. The DBS samples will be sent to CDC laboratories in the United States. The specimens will be tested using a microneutralization assay (polio) and a multiplex bead assay that allows determination of antibodies levels for several VPDs (measles, rubella, tetanus, and diphtheria) and parasitic and neglected tropical diseases (malaria, lymphatic filariasis, trachoma, yaws) for testing on dried blood spots.

### **Study Design**

For purposes of this vaccination assessment, the camps will be divided into the following: Kutupalong Registered Camps, Nayapara Registered Camps, and the informal/makeshift settlements. Surveys within the registered refugee camps (Kutupalong and Nayapara) will apply simple random sampling of households. The survey in the informal/makeshift settlements will use a three-stage cluster sampling design. Children aged 6 months–14 years will be eligible to participate. There are no exclusion criteria.

## **I. Kutupalong and Nayapara Refugee Camps (Simple Random Sampling)**

### **a. Household Selection**

The most up-to-date lists of registered refugees/households will be used to randomly select households 625 households in both Kutupalong and Nayapara Refugee camps.

### **b. Child selection**

During data collection, team members will generate a line list of children in the household aged 6 months–6 years and 7 years–14 years, ordered youngest to oldest. The team will select one child randomly (using simple random sampling) from each age group using a random number generator. Children will be assigned a unique study ID. The caregiver of the selected child(ren) will be consented, enrolled, and interviewed (if consent obtained) using the vaccination coverage assessment questionnaire. DBS samples will also be collected on selected children aged 1y–14y.

### **c. Sample size:**

Logistics and available resources determined that the maximum number of households that can be visited by the field teams is 625 households in both Kutupalong and Nayapara camps. To estimate the expected number of children enrolled we made the following assumptions (Table 1):

- 65% of households will have at least one child aged 6m–6y (for DBS calculations, 60% will have a child aged 1y–6y) and 65% of households will have at least one child aged 7y–14y
- Household non-response rate (i.e., no one home) is 20%
- Child non-response rate (e.g., refusal, child absent from home) is 1% for all children for the survey component of the assessment (primary respondent for the questionnaire is the mother or caregiver); for DBS specimen collection, non-response is estimated at 10% for children 1y–6y and 30% for children aged 7y–14y
- Coverage for 3 pentavalent doses and the proportion of children with protective antibody levels for tetanus is 50%

Given these assumptions, the expected number of children enrolled for the survey is 322 children aged 6m–6y and 322 children aged 7y–14y in each of the camps (Table 1). This results in a 95% Wilson-Score confidence with precision of 5.6% in each age group. The expected number of enrolled children for DBS is 270 children aged 1y–6y and 228 children aged 7y–14y in both the Kutapalong and Nayapara camps (Table 1); precision is 6.1% and 6.7% in each age group, respectively.

The expected total number of children enrolled in both Kutupalong and Nayapara camps is 1,288 for the survey; among these children, 996 will be enrolled for DBS specimen collection.

Table 1. Kutupalong and Nayapara sample size calculations

| Component       | Age group | # Households Visited | Proportion of households with an eligible child | Household Non-response (i.e., no one home) | Child Non-response (i.e., refusal, not home) | # children expected to be enrolled | Coverage/ seroprevalence | Precision |
|-----------------|-----------|----------------------|-------------------------------------------------|--------------------------------------------|----------------------------------------------|------------------------------------|--------------------------|-----------|
| Coverage survey | 6m–6y     | 625                  | 65%                                             | 20%                                        | 1%                                           | 321.8                              | 50%                      | 5.6%      |
| Coverage survey | 7y–14y    | 625                  | 65%                                             | 20%                                        | 1%                                           | 321.8                              | 50%                      | 5.6%      |
| DBS             | 1y–6y     | 625                  | 60%                                             | 20%                                        | 10%                                          | 270.0                              | 50%                      | 6.1%      |
| DBS             | 7y–14y    | 625                  | 65%                                             | 20%                                        | 30%                                          | 227.5                              | 50%                      | 6.7%      |

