**d. Sample size for makeshift camps:**

Thirteen (13) households in 56 clusters will result in a total of 728 households visited. To estimate the expected number of children enrolled we made the following assumptions (Table 1):

- 65% of households will have at least one child aged 6m–6y (for DBS calculations, 60% will have a child aged 1y–6y) and 60% of households will have at least one child aged 7y–14y
- Household non-response rate (i.e., no one home) is 5%
- Child non-response rate (e.g., refusal, child absent from home) is 1% for all children for the survey component of the assessment (primary respondent for the questionnaire is the mother or caregiver); for DBS specimen collection, non-

response is estimated at 10% for children 1y–6y and 20% for children aged 7y–14y

- Coverage for 3 pentavalent doses and the proportion of children with protective antibody levels for tetanus is 50%

Given these assumptions, the expected number of children enrolled for the survey is 445 children aged 6m–6y and 411 children aged 7y–14y in the settlements (Table 1). With a design effect of 1.7 (6m–6y) and 1.6 (7y–14y), this results in a 95% Wilson-Score confidence with precision of 6.2% in both age groups. The enrolment for DBS is 374 children aged 1y–6y and 332 children aged 7y–14y in the settlements (Table 1); the design effect is 1.6 and 1.5, respectively, resulting in a precision of 6.5% (1y–6y) and 6.7% (7y–14y).

The expected total number of children enrolled in the makeshift settlements is 856 for the survey; among these children, 706 will be enrolled for DBS specimen collection.

Table 3. Makeshift camp sample sizes:

| Component       | Age group | # Clusters | # Housholds per cluster | Proportion of households with an eligible child | Household Non-response (i.e., no one home) | Child Non-response (i.e., refusal, not home) | # children expected to be enrolled | Design effect** | Precision |
|-----------------|-----------|------------|-------------------------|-------------------------------------------------|--------------------------------------------|----------------------------------------------|------------------------------------|-----------------|-----------|
| Coverage survey | 6m–6y     | 56         | 13                      | 65%                                             | 5%                                         | 1%                                           | 445.0                              | 1.7             | 6.2%      |

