## **Data Collection, Management and Analysis Plan**

Data collection will take place in Kutupalong refugee camp over the course of about 1 week, in makeshift and informal settlements over the course of 3–4 weeks, and Nayapara refugee camp over the course of about 1 week.

Data will be collected on tablets (Lenovo). Data will be uploaded daily to a Kobo server to enable remote monitoring of data quality. All teams will carry hard copies of the questionnaires as back-ups in case the tablet fails at any point.

A daily random check of entered data will be conducted by the survey manager. Team leaders with respective program personnel will ensure quality data collection at field level.

Vaccination coverage, seroprevalence and respective 95% confidence intervals will be estimated for 6m–6yr old children and 7–14yr old children using survey methods that account for the cluster design and sampling weights.

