| 11                                | Vaccination card                                       | n/% for each antigen                                   | Overall, by camp & age group           |
| 12                                | Disease (malaria symptoms, measles, diphtheria)        | n/% by disease/symptoms                                | Overall, by camp & age group           |
| 13                                | Map of vaccine coverage                                | GPS points for mapping each coverage of antigens       | By camp & age group                    |
| Dried blood spot collection       |                                                        |                                                        |                                        |

| # | Result               | Analysis                                                | Details                                   |
|---|----------------------|---------------------------------------------------------|-------------------------------------------|
| 1 | Denominators         | n/% pricked, refused, not present, failed:
flowchart | Overall, by camp, day, team,
age group |
| 2 | DBS vaccine immunity | n/% coverage for each antigen,
table/graph           | Overall, by camp & age group              |

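### About 29% (camps) and 19% (settlements) of interviewed 7–14-year-olds are expected to give no blood, and the stated seroprevalence method names no response adjustment, so primary estimates could be biased

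*Protocol*

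**What the plan says.** - **Registered camps** (Protocol section 5, I.c Sample size). Interview non-response "is 1% for all children for the survey component of the assessment (primary respondent for the questionnaire is the mother or caregiver". For blood, "for DBS specimen collection, non-response is estimated at 10% for children 1y–6y and 30% for children aged 7y–14y".
- **Settlements** (II.d Sample size for makeshift camps). Interview non-response is again 1%; DBS non-"response is estimated at 10% for children 1y–6y and 20% for children aged 7y–14y".
- **Who is pricked** (I.b and II.c, child selection). Blood is taken from the selected children aged 1–14 y. No further random draw is described, and the sample size tables contain no subsampling factor.
- **Estimation** (Data Collection, Management and Analysis Plan). Coverage and seroprevalence are to be estimated "using survey methods that account for the cluster design and sampling weights".
- **Tabulation** (section 10, Analysis plan, dried blood spot part). Row 1 is a flowchart: "n/% pricked, refused, not present, failed". Row 2 gives number and percentage immune per antigen, overall and by camp and age group. No comparison of children with and without blood, response weight or imputation is named.
- **Data in hand** (section 10, household survey part). Demographics, arrival date when available, doses, campaign participation and card data are listed. These come from the interview, so they would also exist for an interviewed child without blood.

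Protective titres at 1–6 y and at 7–14 y are primary objectives (section 3).

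**The concern.** A caregiver can answer for a child who is out or unwilling, but the child has to be present and agree for the finger-prick. At 7–14 y the interview and blood rows of the tables share the same households, eligibility and household non-response. The whole gap between them is therefore refusal or absence by the child, not a planned random subsample.

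If giving blood is related to vaccination, or to age within the broad 7–14 y band, the children pricked do not represent those selected. Sampling weights correct for unequal selection, not for this. Reporting by camp and age group separates the cells in which the protocol expects response to differ, but does nothing about selective response within a cell. At stake are primary estimates meant to show how many children remain unprotected.

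**Working it through.** **1. Reproduce the plan's counts at 7–14 y.** Expected n = households × share with an eligible child × (1 − household non-response) × (1 − child non-response). Inputs are from I.c, II.d and the sample size tables.

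| | Interview | Blood |
|---|---|---|
| Each camp | 625 × 0.65 × 0.80 × 0.99 = 321.75 (stated 321.8) | 625 × 0.65 × 0.80 × 0.70 = 227.5 (stated 227.5) |
| Settlements | 728 × 0.60 × 0.95 × 0.99 = 410.8 (stated 410.8) | 728 × 0.60 × 0.95 × 0.80 = 332.0 (stated 332.0) |

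The stated 6.7% precision at 7–14 y is also consistent with these reduced blood numbers. A continuity-corrected Wilson interval at 50% gives 6.66% in a camp. In the settlements it gives 6.75%, or 6.64–6.86% over the rounding of the design effect of 1.5. The question is bias, not a wrong sample size.

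**2. Share of interviewed children without blood.**
- Camp: 1 − 227.5/321.75 = 29.3% (94 children).
- Settlements: 1 − 332.0/410.8 = 19.2% (79 children).
- All sites at 7–14 y: 1 − 787/1055 = 25.4%.
- At 1–6 y, in either setting: 1 − 0.90/0.99 = 9.1%.

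**3. Possible bias.** Relative to all interviewed children, bias = missing share × d, where d is the difference in seroprotection between children with and without blood. The documents give no value for d, so a range is assumed. The sign of the bias follows the sign of d. Coverage of the nominal 95% interval uses a normal approximation, Φ(1.96 − b/SE) − Φ(−1.96 − b/SE). At 50% seroprevalence SE = √(0.25/227.5) = 3.3 points in a camp and √(0.25 × 1.5/332.0) = 3.4 points in the settlements.

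| Assumed d (points) | Camp: bias | Camp: coverage | Settlements: bias | Settlements: coverage |
|---|---|---|---|---|
| 5 | 1.5 | 93% | 1.0 | 94% |
| 10 | 2.9 | 86% | 1.9 | 91% |
| 15 | 4.4 | 74% | 2.9 | 86% |
| 20 | 5.9 | 58% | 3.8 | 79% |

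At 1–6 y the same range of d gives 0.091 × 5 to 0.091 × 20, or 0.5 to 1.8 points.

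**4. What response weighting could do (illustration, all inputs assumed).** Take a camp where half the interviewed children are reported as dosed. Seroprotection is 70% in the dosed and 30% in the others, so the true value is 50.0%. Blood response is 80.7% and 60.7%, which averages the expected 70.7%.
- Unadjusted: (0.5 × 0.807 × 0.70 + 0.5 × 0.607 × 0.30)/0.707 = 52.8%.
- Weighted by 1/response within dose status: 0.5 × 0.70 + 0.5 × 0.30 = 50.0%.
- Variance factor from the weights: (0.5/0.807 + 0.5/0.607) × 0.707 = 1.02.

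The correction is complete here only because dose status is assumed to explain all of the selective response.

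**The case against.** **Silence is not exclusion.** A reader might infer that sampling weights alone will be used. The protocol does not say how the weights are built, and a statistical analysis plan that is not shown could include a response factor. That stands as a limit. But the protocol states its estimator and carries its own analysis plan, which foresees the loss, counts it and then moves to percentage immune. Naming the adjustment there improves a primary estimate.

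**The direction is unknown.** A reader might infer that seroprotection will be overstated because absent or refusing children also missed campaigns. The documents do not show this. The bOPV campaigns listed in section 2 targeted children under 5 or under 7 years, so missing them would not explain polio seronegativity at 7–14 y. Measles was circulating, so an unvaccinated child may be immune through infection. The flowchart also has a category for failed pricks, which is neither refusal nor absence. This objection stands in full: only a possible bias can be claimed.

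**The covariates are weak.** Sections 1 and 4 say that few campaign cards are kept and doses are hard to recall, and section 10 lists arrival date only if available. This stands too. An interview will exist for nearly every selected child in a responding household, but adjustment on its answers would be partial.

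**Coverage and immunity can still be compared.** A reader might infer that the two results will describe different children and so cannot be set side by side. The documents do not support that: children giving blood are a subset of those interviewed, so both can be examined in the same children.

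**The bias is smaller than the precision.** Every value in the assumed range is below 6.7 points. That is true, but bias adds to sampling error, and the stated precision contains none of it.

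**Conclusion.** The point holds as a risk of bias in primary estimates, with an inexpensive partial remedy that the protocol does not name. The non-response shares, 29% in each registered camp and 19% in the settlements at 7–14 y, follow directly from the protocol's own assumptions. The bias does not. It rests on an assumed 5- to 20-point difference in seroprotection, which gives 1.5 to 5.9 points in a camp and 1.0 to 3.8 in the settlements, in either direction. At 1–6 y the issue is smaller. The stated sample sizes stand. The change is worth making before analysis; the gap does not invalidate the survey.

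**What to change.** In the Data Collection, Management and Analysis Plan and in the blood-spot rows of section 10, state the following.

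- For seroprevalence, multiply the sampling weight by the inverse of the estimated probability of giving blood among interviewed children aged at least 1 year. Estimate it within age group and stratum, by weighting classes or logistic regression.
- Use age, sex and reported campaign doses as predictors, plus card seen and arrival period where recorded, with a category for missing values.
- Tabulate interview characteristics by whether blood was obtained.
- Report the base-weighted estimate beside the adjusted one.

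This needs no new data and little analysis time. The price is a somewhat larger variance: 2% in the illustration, with 2–10% a reasonable assumed range when more predictors are used. The adjustment removes only the bias explained by recorded, partly recall-based variables. It does not address household non-response, assumed at 20% in the camps, because no interview exists for those households. The report should say so.
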